## Abstract

**Background:**

Currently, the impact of drug therapies on neurodegenerative conditions is limited. Therefore, there is a strong clinical interest in non-pharmacological interventions aimed at preserving functionality, delaying disease progression, reducing disability, and improving quality of life for both patients and their caregivers. This longitudinal multicenter Randomized Controlled Trial (RCT) applies three innovative cognitive telerehabilitation (TR) methods to evaluate their impact on brain functional connectivity reconfigurations and on the overall level of cognitive and everyday functions.

**Methods:**

We will include 110 participants with mild cognitive impairment (MCI). Fifty-five participants will be randomly assigned to the intervention group who will receive cognitive TR via three approaches, namely: (a) Network-based Cognitive Training (NBCT), (b) Home-based Cognitive Rehabilitation (HomeCoRe), or (c) Semantic Memory Rehabilitation Training (SMRT). The control group (*n* = 55) will receive an unstructured home-based cognitive stimulation. The rehabilitative program will last either 4 (NBTC) or 6 weeks (HomeCoRe and SMRT), and the control condition will be adapted to each TR intervention. The effects of TR will be tested in terms of Δ connectivity change, obtained from high-density electroencephalogram (HD-EEG) or functional magnetic resonance imaging at rest (rs-fMRI), acquired before (T0) and after (T1) the intervention. All participants will undergo a comprehensive neuropsychological assessment at four time-points: baseline (T0), within 2 weeks (T1), and after 6 (T2) and 12 months (T3) from the end of TR.

**Discussion:**

The results of this RCT will identify a potential association between improvement in performance induced by individual cognitive TR approaches and modulation of resting-state brain connectivity. The knowledge gained with this study might foster the development of novel TR approaches underpinned by established neural mechanisms to be validated and implemented in clinical practice.

**Clinical trial registration:** [https://classic.clinicaltrials.gov/ct2/show/NCT06278818], identifier [NCT06278818].

## Introduction

Neurodegenerative diseases, such as Alzheimer’s disease (AD) and, in some cases Parkinson’s disease (PD), are characterized by progressive cognitive decline (Gonzales et al., 2022). Mild cognitive impairment (MCI) could represent a prodromal phase of different forms of dementia, in which, subjects present with objective and measurable cognitive deficits, although they maintain independence in daily-life activities (Yaffe et al., 2006).

No consensus has been reached on the effects of non-pharmacological interventions to contrast cognitive decline, but there is a general agreement that these approaches are more likely to succeed the sooner they are implemented and the more accurately they act on the cognitive domains affected by neurodegenerative diseases (Yao et al., 2020). Previous evidence showed effects of both single-domain and multi-domains cognitive rehabilitation on brain functionality in MCI (Rosen et al., 2011; Hampstead et al., 2012; Suo et al., 2016; Barban et al., 2017; De Marco et al., 2018).

Recently, several non-pharmacological interventions have been implemented in telerehabilitation (TR). TR is a promising approach as it offers and facilitates rehabilitative services to a broader population, and it has the potential to lower costs for both healthcare providers and patients (Kruse et al., 2020). However, there are still some aspects that need to be addressed in the implementation of TR for older adults with early cognitive deficits, including issues related to self-confidence, digital literacy, user experience, frequency of use, and dependence on guidance (Md Fadzil et al., 2022).

Randomized Controlled Trials (RCT) with adequate sample sizes and trial methodologies aimed at mitigating bias are necessary to assess the efficacy of TR for individuals at risk of dementia.

Specifically, in the current longitudinal multicenter RCT, we will apply three different cognitive TR approaches to patients with MCI due to neurodegenerative diseases. This clinical trial protocol aims to establish the feasibility and efficacy of three different cognitive TR approaches, and their impact on brain functional connectivity/synchronization, assessed by means of either high-density electroencephalogram (HD-EEG) or functional magnetic resonance imaging at rest (rs-fMRI).

The first TR approach is the Network-based Cognitive Training (NBCT), a cognitive training specifically designed to promote the co-activation of multiple brain areas (i.e., central nodes), modulating the functional connectivity of specific resting state networks (RSNs). This rehabilitation package has been used in face-to-face mode on a sample of healthy participants, in whom a rehabilitation-induced “up-regulation” effect of functional connectivity of the rear central nodes of the default mode network (DMN) was observed (De Marco et al., 2017). Subsequently, this training approach has been tested in amnestic MCI (De Marco et al., 2018), PD with MCI (Venneri et al., 2021) and in patients with relapsing–remitting multiple sclerosis who complained of mild cognitive deficits (Manca et al., 2021). Notably, the NBCT program will be implemented on a TR platform (i.e., Khymeia) and can be administered through a virtual connection. A link will be provided for each rehabilitation session, and this allows participants to access and use the TR protocol through a web browser on their personal computer, tablet, or mobile phone. This approach offers many advantages in terms of practicality, ease of use and accessibility for study participants.

The second TR approach is the Home-based Cognitive Rehabilitation (HomeCoRe) system. This is a software for cognitive TR especially developed for the initial stages of decline (amnestic MCI, MCI-PD, mild AD). HomeCore has been developed starting from a validated in-person computer-based cognitive intervention (CoRe) the efficacy of which in the short and long term has been verified in outpatients’ hospital services also in combination with neuromodulatory techniques (Alloni et al., 2017, 2018; Bernini et al., 2019, 2021, 2023; Rodella et al., 2022). HomeCoRe is an adaptive patient-tailored treatment focused on training memory and logical-executive functions that provides a Weighted Score of performance for each exercise and each session to monitor patients’ progress remotely and to adjust automatically the level of exercise difficulty accordingly. This strategy is applied to avoid either over- or under-stimulating patients. The software provides an easy-to -access platform that patients interact with via a touch screen. Usability and acceptance of HomeCoRe have already been tested in a small group of patients with MCI due to a neurodegenerative disease (Bernini et al., 2023).

The third TR approach is the Semantic Memory Rehabilitation Training (SMRT). This approach has been developed considering the crucial role that processing of semantic aspects of episodic information plays in long-term episodic memory processes (Craik and Lockhart, 1972), and based on recent evidence indicating early involvement of semantic memory in preclinical forms of Alzheimer’s disease (Wright et al., 2022). MCI patients will be trained to generate as many semantic features as possible they can in response to the visual presentation of objects from multiple semantic categories. The dual objective of this approach is to improve semantic memory processes and, capitalizing upon the richer semantic encoding of episodic events, make the retrieval processes more efficient. The protocol is administered through TR using a specific device with constant assistance from an online therapist.

## Methods and analysis

### Study design

The proposed study is a prospective single-blind RCT, involving different Italian centers (Università di Pavia, AUSL Azienda Ospedaliero Universitaria di Parma, IRCCS Fondazione Santa Lucia di Roma, and IRCCS Istituto delle Scienze Neurologiche di Bologna). A CONSORT flow chart for enrolment and randomization is shown in Figure 1. After recruitment, participants will be contacted and will undergo in-person baseline assessment (T0) using the below-listed tests (see Participants’ evaluation section and Table 1). Participants who meet inclusion criteria will be enrolled and randomized to the active or control interventions (Table 1).

**Figure 1 fig1:**
[figure not shown]
CONSORT flow chart for enrolment and randomization.

**Table 1 tab1:** Characteristics of included interventions.

Approach	Network-Based Cognitive Training (NBCT)	Home-based Cognitive Rehabilitation (HomeCoRe)	Semantic Memory Rehabilitation Training (SMRT)	Unstructured Home-based Cognitive Stimulation (Sham Comparator)
Participants	40 participants with MCI randomly allocated to NBCT.	5 participants with MCI randomly allocated to HomeCoRe.	10 participants with MCI randomly allocated to SMRT.	55 MCI, randomly assigned to one of three control groups (CG): CG for NBCT (*n* = 40), CG for HomeCoRe (*n* = 5), CG for SMRT (*n* = 10).
Interventions	Cognitive training specifically designed to promote cognitive functions in early stages of neurodegenerative conditions.	Cognitive training specifically designed to promote cognitive functions in early stages of neurodegenerative conditions.	Cognitive training specifically designed to promote cognitive functions in early stages of neurodegenerative conditions.	This activity is commonly used as a control condition to test the efficacy of innovative rehabilitative treatments.
Outcome measures	Primary outcome: Assessment of resting-state functional connectivity at baseline (T0) and at the end of NBCT (T1 after 4 weeks). Secondary outcome: Global cognitive and neuropsychological changes at T1, T2, and T3 vs. T0 when applicable according to Table 1. Secondary outcome measures will also include participant-centered assessment at T1.	Primary outcome: Assessment of resting-state functional connectivity at baseline (T0) and at the end of HomeCoRe (T1 after 6 weeks). Secondary outcome: Global cognitive and neuropsychological changes at T1, T2, and T3 vs. T0 when applicable according to Table 1. Secondary outcome measures will also include participant-centered assessment at T1.	Primary outcome: Assessment of resting-state functional connectivity at baseline (T0) and at the end of SMRT (T1 after 6 weeks). Secondary outcome: Global cognitive and neuropsychological changes at T1, T2, and T3 vs. T0 when applicable according to Table 1. Secondary outcome measures will also include participant-centered assessment at T1.	Primary outcome: Assessment of resting-state functional connectivity at baseline (T0) and at the end of sham intervention (T1 after 4 or 6 weeks). Secondary outcome: Global cognitive and neuropsychological changes at T1, T2, and T3 vs. T0 when applicable according to Table 1. Secondary outcome measures will also include participant-centered assessment at T1.

The primary active condition involves administering the NBCT protocol to 40 subjects with MCI across all included centers. The HomeCoRe protocol, involving 5 subjects, will be conducted exclusively in Pavia, while the SMRT protocol, involving 10 subjects, will be implemented only in Rome. The control condition consists in an unstructured home-based cognitive stimulation, involving 60 min of daily activities, with MCI sample size, frequency and overall treatment duration adapted to the experimental treatment of comparison. For each session, newspaper articles will be provided for the patient to read and summarize in a diary by answering specific questions. The protocol is administered remotely through TR with online assistance from a therapist.

Each patient will undergo brain rs-fMRI or HD-EEG acquisitions before (T0) and after (T1) active or control interventions.

Follow-up in-person neuropsychological assessments will be scheduled within 2 weeks from the end of the rehabilitation program (T1), and after 6 (T2) and 12 months (T3).

### Control for confounding variables and biases

After baseline assessment, patients included in the study will be randomly allocated to two groups in a ratio of 1:1 based on active and control interventions, controlling for sex and education levels. We will generate random numbers with a computer algorithm^1^ from a uniform distribution in the range 0–1, dividing the range into two equal intervals and assigning each participant to the group corresponding to the sampled number (1,1 ratio). Stratification will be employed to ensure equal distribution of participants within each stratum (e.g., blocks based on sex and education level), and block randomization will be used within each block. Propensity score matching will be applied using logistic regression and matching participants based on similar scores, to ensure comparable groups.

Neuropsychologists carrying out cognitive evaluations will be blinded to group allocation to prevent bias. They will receive appropriate instruction and guidance regarding all assessment procedures and outcome parameters. Reminders (e.g., written reminders, phone calls, and email messages) for each visit will be sent to all participants to ensure compliance and complete data collection.

Not all outcome measures will be administered at each time point (summary in Table 2).

**Table 2 tab2:** Evaluation battery across testing sessions.

	T0	T1	T2	T3

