### Participants and eligibility criteria

Participants will be recruited from the Cognitive Disorders and Dementia Centre outpatient services and Movement Disorders and Neurorehabilitation Unit of IRCCS Mondino Foundation (Pavia, Italy), from the Unit of Neurology, University-Hospital of Parma (Parma, Italy), from the Neurological Clinic and NEUROMET of the IRCCS Institute of Neurological Sciences of Bologna-University of Bologna and the IRCCS S. Lucia Foundation of Rome. These patients will be asked to participate as volunteers in the study. Following their consent, they will be screened for eligibility criteria through a clinician evaluation carried out by an expert neurologist.

The inclusion criteria for participants will be:

Diagnosis of amnestic MCI (Petersen et al., 1999) or Parkinson’s disease with MCI (Litvan et al., 2011);Aged between 60 and 85 years;Years of education ≥5;Clinical Dementia Rating (CDR) (Hughes et al., 1982) score = 0.5.The exclusion criteria will be:Mini-Mental State Examination (MMSE) score < 20;Presence of cognitive impairment secondary to an acute or general medical disorder (e.g., brain trauma, small vessel disease, vascular impairment or tumor);Presence of severe neuropsychiatric conditions (e.g., mood and behavioral disorders);Presence of severe sensory disorder (e.g., deafness or blindness) or motor impairments that prevent trunk control and/or sitting position;Current cognitive treatments;Lack of family support.

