#### Secondary objective analysis plan

Differences in global cognitive and neuropsychological performance scores, as well as caregiver burden assessments will be independently assessed using a two-way repeated measures ANOVA model, including assessment times and the TR interventions (active vs. control) as factors. The interaction between time and type of TR intervention will be investigated. To explore the variability in the trajectories of global cognitive and neuropsychological performance scores, individual items will be independently assessed using repeated measures linear mixed models. The time elapsed between assessments will be used to estimate the monthly rate of change, considering the type of TR intervention (active vs. control) as a main effect.

Furthermore, a linear correlation analysis will be applied to test the relationship between changes in connectivity from T0 to T1 and cognitive change over time. As mentioned above, the analyses will be conducted separately for each type of treatment/outcome and individual performance parameter.

We will re-run all the aforementioned analyses, stratifying by MCI subtype (aMCI and PD-MCI), to evaluate the disease-specific effects of TR on brain connectivity.

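### Every analysis is to be repeated by MCI subtype, yet subtype is not among the allocation factors named, so its balance between arms is left to chance

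*Protocol article*

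**What the plan says.** Participants and eligibility criteria admits two conditions, "Diagnosis of amnestic MCI" or "Parkinson’s disease with MCI", with no quota or expected mix.

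Control for confounding variables and biases sets allocation as follows: "patients included in the study will be randomly allocated to two groups in a ratio of 1:1 based on active and control interventions, controlling for". The factors it then names are sex and education. The strata follow as an illustration: "Stratification will be employed to ensure equal distribution of participants within each stratum (e.g., blocks based on sex and education level". The same section adds propensity score matching without listing the variables in the score. Subtype appears nowhere in it.

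The Primary outcome analysis plan fits a separate model for each programme and lists MCI subtype among seven potential confounders to be used as covariates. The Secondary objective analysis plan specifies a repeated measures ANOVA whose named factors are time and arm, and then states: "We will re-run all the aforementioned analyses, stratifying by MCI subtype (aMCI and PD-MCI), to evaluate the disease-specific effects of TR on brain connectivity".

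Table 1 gives 40 v 40 for NBCT, 10 v 10 for SMRT and 5 v 5 for HomeCoRe. Under Study design, SMRT runs only in Rome and HomeCoRe only in Pavia.

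**The concern.** Subtype is known before randomisation, because it is the first inclusion criterion. It is also the only factor by which the plan repeats all of its analyses. A factor with that role is a natural candidate for stratification, but the two factors named are others.

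Three things are at stake.

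- **Small programmes.** SMRT and HomeCoRe are analysed on their own, and the arms can differ widely in disease mix there.
- **Secondary outcomes.** The ANOVA names no subtype term, so an imbalance there goes unadjusted.
- **Subtype re-runs.** If one arm of a programme has no PD-MCI patients, the planned PD-MCI comparison cannot be made. No covariate can repair that.

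**Working it through.** The document gives no figure on subtype balance, so there is none to reproduce.

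**Inputs.** Arm sizes 40, 10 and 5 come from Table 1. Assumed, because the document does not give them: a PD-MCI share of 20%, 30% or 50%; four equally likely sex-by-education strata; blocks of 4.

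**1. Simple 1:1 allocation with fixed arms.** With N patients, K of them PD-MCI, and n = N/2 per arm, the PD-MCI count X in one arm is hypergeometric(N, K, n). The difference in share is |2X − K|/n.

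| Programme | Event | 20% | 30% | 50% |
|---|---|---|---|---|
| NBCT (K = 16, 24, 40 of 80) | 10 points or more | 40% | 46% | 50% |
| NBCT | 20 points or more | 5% | 9% | 12% |
| SMRT (K = 4, 6, 10 of 20) | 20 points or more | 58% | 63% | 66% |
| SMRT | 40 points or more | 9% | 14% | 18% |
| HomeCoRe (K = 2, 3, 5 of 10) | all PD-MCI in one arm | 44% | 17% | 1% |

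The mean difference is 0 in every row. In SMRT, 20 points is the smallest difference possible when K is even and the arms are 10 v 10, so that row is the chance of any split other than an equal one.

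**2. Blocks of 4 within sex by education (20,000 simulated trials).** The chance of 10 points or more in NBCT is 33%, 39% and 44%. It can fall to about 28% at the low end under other assumptions about the strata; a run with subtype related to the strata gave 29% at a 20% share. Part of the drop from step 1 is rounding: incomplete blocks leave slightly unequal arms, and a difference of four patients then just misses 10 points. With strata of exactly 20 people each, the figures return to 41%, 47% and 50%.

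**3. Subtype added to the NBCT blocks.** The chance of 10 points or more falls to 0.4-0.7%.

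**4. Small programmes, 20 points or more.** Adding subtype to sex and education lowers SMRT from 42-51% to 20-25%, but HomeCoRe only from 47-77% to 46-70%, because eight strata cannot be filled by 10 people. With subtype as the sole factor:

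- SMRT falls to 0% with blocks of 2, and to 0%, 6% and 6% with blocks of 4.
- For HomeCoRe, the chance that all PD-MCI patients share an arm falls to 0% with blocks of 2. With blocks of 4 it is 33% for 2 of 10, and 0% for 3 or 5 of 10.

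**5. What the covariate can do.** In NBCT at a 30% share, with a subtype effect of 0.5 or 1.0 SD, simulated type I error is 4.9-5.0% unadjusted and 5.0-5.1% adjusted, with mean bias about 0 either way. Adjustment lowers the SD of the estimate from 0.228 to 0.224 (0.5 SD) or from 0.246 to 0.226 (1.0 SD). The small programmes are single-centre, so six listed covariates remain. With an intercept, arm and one term per covariate, a change-score model has 8 parameters. That leaves 20 − 8 = 12 residual degrees of freedom in SMRT and 10 − 8 = 2 in HomeCoRe.

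**6. Power of the re-runs.** At d = 0.5, two-sided 5%, power is 15% with 8 per arm, 22% with 12 and 34% with 20.

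**The case against.** The case against has several parts.

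- **The list of strata is illustrative, and this is a condensed article.** This stands. The text does not show that subtype is excluded. But the sentence on allocation itself names sex and education without that qualifier, and subtype is named nowhere in the section.
- **A reader might infer that subtype is confounded with arm.** The document does not support that. Allocation is random, so imbalance arises by chance, averages zero and leaves type I error nominal (step 5).
- **The primary model already adjusts for subtype.** This stands for NBCT, the only comparison with a power calculation. It does not reach the secondary ANOVA as described, and it is weak in the small programmes. Propensity matching on unlisted variables cannot supply PD-MCI patients to an arm that has none.
- **Sampling noise exceeds the imbalance.** This also stands. If the subtype effect on change is 0.5 SD (an assumption), 10 points in NBCT shifts the estimate by 0.10 × 0.5 = 0.05 SD, against a standard error of sqrt(2/40) = 0.22 SD. In SMRT, 20 points gives 0.10 SD against sqrt(2/10) = 0.45. In HomeCoRe, three PD-MCI patients in one arm gives 0.6 × 0.5 = 0.30 SD against sqrt(2/5) = 0.63. The outcome is a change score, so stable disease differences cancel. It is therefore not shown that an imbalance would pass for a treatment effect.
- **The PD-MCI share is assumed.** It is, and it may differ by centre: a movement disorders unit is named only for Pavia, whereas SMRT runs in Rome.

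A reader might also infer that SMRT should take only aMCI, since its rationale is partly "based on recent evidence indicating early involvement of semantic memory in preclinical forms of Alzheimer’s disease". The Introduction first gives a more general basis, the part that semantic processing plays in episodic memory, and speaks of MCI patients without distinction. Restricting SMRT would be an eligibility preference and is no part of this point.

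**Conclusion.** The point holds as a cheap improvement in design, not as a source of bias. The plan gives subtype a central role in the analysis and no named role in allocation. Active-control balance across and within subtypes is therefore left to chance.

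For NBCT, a 10-point or larger difference is about as likely as 28-50%, depending on the assumed share and blocking; the covariate largely absorbs it in the primary model. The exposed parts are the secondary ANOVA, the two small programmes and the subtype re-runs, which could have an empty arm.

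The sizes rest on assumed values for the PD-MCI share, block size and number of strata. That disease affects change in connectivity more than sex or schooling does is plausible, but the document does not show it.

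**What to change.** Before enrolment:

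1. Name MCI subtype (aMCI or PD-MCI) as a stratification factor for the blocked 1:1 allocation within each programme. In NBCT use it with sex and education; in SMRT and HomeCoRe use it in their place.
2. Use short blocks and conceal their size. Blocks of 2 balance best but are the most predictable.
3. Add subtype as a term in the secondary models.

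The cost is a revised allocation list and one model term, with no extra patients or procedures. NBCT gets more and smaller strata (2 × 2 × 2 = 8 if education has two levels). Sex and education are no longer balanced by design in the two small programmes. Stratification will not make the small subtype re-runs informative: three PD-MCI patients can split no better than 2:1.

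### The allocation section gives two conflicting randomisation rules and adds a propensity-score matching step that has no valid role in a 1:1 randomised comparison

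*Protocol article*

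**What the plan says.** In *Control for confounding variables and biases*, participants are "randomly allocated to two groups in a ratio of 1:1 based on active and control interventions"; sex and education are to be taken into account. The section then describes three procedures in turn.

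- **A uniform draw.** Random numbers between 0 and 1 are generated, "dividing the range into two equal intervals and assigning each participant to the group corresponding to the sampled number (1,1 ratio").
- **Stratified blocks.** The next sentence opens with a different rule: "Stratification will be employed to ensure equal distribution of participants within each stratum (e.g., blocks based on sex and education level"). Inside those strata, according to the same sentence, "block randomization will be used within each block".
- **Matching.** The last step is stated without further detail: "Propensity score matching will be applied using logistic regression and matching participants based on similar scores, to ensure comparable groups".

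The section does not say which of the first two governs. For the matching it names the model (logistic regression) but no covariates, caliper, ratio or rule for unmatched patients.

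Table 1 (*Characteristics of included interventions*) fixes sizes by programme. On the active side these include "40 participants with MCI randomly allocated to NBCT" and "10 participants with MCI randomly allocated to SMRT", with 5 for HomeCoRe. The controls mirror them: "CG for NBCT (*n* = 40), CG for HomeCoRe (*n* = 5), CG for SMRT (*n* = 10"). Under *Study design*, NBCT runs at all centres, HomeCoRe only in Pavia and SMRT only in Rome. The primary outcome analysis plan models each programme separately and lists seven potential confounders as covariates: centre, MCI subtype, age, sex, functional activities, pharmacological treatment and cognitive reserve.

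**The concern.** The two allocation rules are different algorithms. In a uniform draw each assignment is independent of the ones before it. In a permuted block the later assignments are constrained by the earlier ones. A person building the list cannot do both, and the choice decides whether the Table 1 sizes are protected.

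Matching is a tool for non-randomised comparisons. A propensity score models group membership, so it can be fitted only after groups exist. It therefore cannot be a way of forming randomised pairs beforehand. Once groups have been formed by 1:1 randomisation, the fitted score reflects chance imbalance only, and the covariates listed for the outcome model already address that. If matching alters anything, it does so by leaving out people who were randomised. The comparison is then no longer the one that randomisation protects. Because each programme is analysed alone, groups of 10 and 5 per arm have little room for such losses.

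**Working it through.** **Inputs from the article.** Arms of 40, 5 and 10 on each side: 40 + 5 + 10 = 55, and 2 × 55 = 110, which agrees with the stated total. Allocation is 1:1 and each programme is modelled separately.

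**Step 1. If the uniform draw is the rule.** With N participants in a programme and probability 0.5 each, the chance of an exact split is P = C(N, N/2) / 2^N, and the expected smaller arm is (N/2)(1 − P). This assumes that each programme recruits its planned total.

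| Programme | N | P(exact split) | Expected smaller arm |
|---|---|---|---|
| NBCT | 80 | 0.089 | 40 × 0.911 = 36.4 |
| SMRT | 20 | 0.176 | 10 × 0.824 = 8.2 |
| HomeCoRe | 10 | 0.246 | 5 × 0.754 = 3.8 |

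All three exact together: 0.0889 × 0.1762 × 0.2461 = 0.0039. For HomeCoRe, a split of 7:3 or worse has probability 2 × (1 + 10 + 45 + 120) / 1024 = 0.34.

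**Step 2. Matching without a caliper.** One-to-one matching keeps as many pairs as the smaller arm has people. With equal arms, all 40 of 40 NBCT pairs are kept, so nobody is lost and group composition does not change. With arms from the uniform draw, the expected number lost is N minus twice the expected smaller arm:

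- NBCT: 80 − 72.9 = 7.1 (9%)
- SMRT: 20 − 16.5 = 3.5 (18%)
- HomeCoRe: 10 − 7.5 = 2.5 (25%)

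**Step 3. Matching with a caliper.** The article gives none, so these settings are assumptions: greedy 1:1 matching, a caliper of 0.2 SD of the logit, equal arms, 2, 5 or 7 independent normal covariates unrelated to arm, and 1,000 simulated trials per setting. Mean pairs are taken over runs in which the model could be fitted.

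| Arms | Mean pairs kept (2, 5, 7 covariates) | Logistic model failed or separated |
|---|---|---|
| 40:40 | 29.4, 28.3, 27.3 | 0%, 0%, 0% |
| 10:10 | 4.9, 4.2, 3.9 | 0%, 3%, 13% |
| 5:5 | 1.6, 1.6, 1.9 | 6%, 71%, 97% |

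In NBCT this is a loss of (40 − 29.4)/40 = 26% to (40 − 27.3)/40 = 32%.

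**Step 4. How many strata blocks can support.** NBCT runs at four centres. Crossing centre with sex and, by assumption, two education levels gives 4 × 2 × 2 = 16 strata, and 80/16 = 5 patients in each on average. With blocks of 2, 4 and 6 in equal-sized strata, simulation gives an exact 40:40 in only about 21% of runs. The SD of the arm difference is about 4, against √80 ≈ 9 for the uniform draw. An unfinished block of 6 can leave an imbalance of at most 3, so the worst case is 16 × 3 = 48 with sixteen strata and 4 × 3 = 12 with centre alone. Blocks help, but only if the strata are few.

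**The case against.** The best defence is that the article also specifies block randomisation, that its strata are introduced only as examples, and that a condensed article may leave the full list of factors to the complete protocol. The analysis plan never mentions a matched set, and it already includes covariate adjustment. Much of this stands, and it limits what can be claimed.

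- A reader might infer that matching is bound to discard patients. The article does not support that: with equal arms and no caliper the loss is zero. Nor does it say that the primary analysis is confined to matched pairs.
- A reader might infer that the planned sizes cannot be reached. Block randomisation can deliver them exactly or nearly so. The probabilities in Step 1 apply only if the uniform draw governs.
- A reader might infer that arm is confounded with centre or programme. It is not. HomeCoRe and SMRT are each single-centre with their own controls, and each programme is modelled separately. In NBCT a uniform draw risks only chance imbalance across centres, and centre is a listed covariate.
- A reader might attach a power loss to the matching. Any figure would rest on an assumed caliper and an unadjusted test, ignoring the covariates and the T0–T1 correlation. Whether 40 per condition is enough is a separate question.

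What the defence does not answer is the text itself. Two incompatible rules are stated without precedence, and the matching sentence is a positive commitment, not an omission. Its mildest reading has no effect and its other readings remove randomised patients.

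**Conclusion.** The point holds as a contradiction in the allocation rule together with a matching step that should not be there. The contradiction and the redundancy of matching follow from the text alone and need no assumption.

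The size is a range, because the settings are unstated. In NBCT the loss runs from 0% (equal arms, no caliper), through about 9% on average (uniform draw, no caliper), to roughly a third (assumed 0.2 SD caliper). In the 5:5 comparison, how often the propensity model fails depends heavily on the assumed number of covariates, but with five or more it fails in most runs. The planned sizes are not assured if the uniform draw is used. They are attainable, or nearly so, if blocks are used with few strata. This should be settled before allocation starts, since the randomisation method cannot be repaired afterwards.

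**What to change.** 1. Delete the propensity-matching sentence. State that all randomised participants are analysed in the group to which they were allocated, with chance imbalance handled by the baseline covariates already listed in the primary outcome analysis plan.
2. Delete the uniform-draw sentence and keep one scheme: computer-generated 1:1 permuted blocks, run separately within each programme and stratified by centre in NBCT.
3. Handle sex and education as model covariates, or through a small number of strata so that blocks can fill. Education is not named in the present covariate list, so it must be added if it stops being a stratum.
4. For HomeCoRe and SMRT, drop centre (it is constant) and prespecify a very short covariate list, since 10 and 20 patients cannot support all the listed variables.

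The cost is a protocol rewording and the setup of the list. The one statistical downside is less exact balance on sex and education.
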